**Diabetes My Way, Oviva, and Changing Health behavioral interventions**
Primary outcomeChange in hemoglobin A_1c_ levels [26,27].Secondary outcomesChanges in body weight or BMI, blood pressure, cholesterol, and smoking [28].Uptake, engagement, user experience, retention, completion [29], and health care use (clinic and hospital attendance and medication use).Impact of primary care staff on knowledge, skills, and confidence in diabetes management [30].Modifying effect of cognitive function [31].

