### Overview of Data Items and Source of Data by Intervention in the Quantitative Study

#### Diabetes My Way

To evaluate the DMW intervention, the University of Manchester will obtain participant data from GP records via DMW, between April 1, 2016, and March 30, 2022. These data will include the following: age, sex, ethnicity, GP postcode (to assess the degree of socioeconomic deprivation) [35], diabetes type and duration, blood pressure, cholesterol, creatinine, estimated glomerular filtration rate (eGFR), smoking and body weight, height, BMI, medication, diabetes clinic attendance in primary care, and hospital visits including emergency visits.

Participant data from DMW or NHS Digital will also include ethnicity (self-provided, sometimes unreliable from primary care due to missing data), user experience or usability, service use (medication, diabetes clinic attendance in primary care, and hospital visits including emergency visits), and website activity.

Data on control participants (not using DMW) will be obtained from NHS Digital, from April 1, 2016, to March 30, 2022, and will include the following: age, sex, ethnicity, GP postcode (to assess socioeconomic deprivation), diabetes type and duration, blood pressure, cholesterol, creatinine, eGFR, smoking and body weight, height, BMI, medication, diabetes clinic attendance in primary care, and hospital visits including emergency visits.

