#### Clinical Data

The clinical data of interest includes age, sex, ethnicity, socioeconomic deprivation, diabetes type, weight, height, BMI, HbA_1c_, blood pressure level, diabetes medication, blood pressure medication, lipid lowering therapy, and service use data (attendance and nonattendance at diabetes clinics and emergency hospital visits) will be obtained from primary care records. Ethnicity will be taken from self-reported data provided at enrollment with DMW (White, South Asian, Black, mixed, or other, if *other* participants will be invited to specify using text). Socioeconomic deprivation will be assessed from the GP postcode to reduce the likelihood of participants being identified.

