#### Biochemical Data

All blood sampling (eg, HbA_1c_ and serum lipids) will be conducted via routine clinical care. Participants who did not have a blood sample taken within the preceding 3-6 months will be advised through a message on the DMW website to arrange a diabetes review (weight, blood pressure, smoking status, medication review, HbA_1c_, and lipids) with their practice team at the time of enrollment in line with standard clinical care according to National Institute for Health and Care Excellence (NICE) guidance 28 [36] Participants will be advised to have repeat weight, blood pressure, medication review, and blood tests every 3-6 months in line with standard clinical care according to NICE guidance 28 [36]. Study participants will not be subject to any investigations outside of their routine care unless clinically indicated. Blood test results will be transferred to DMW from the primary care record.

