### Economic Evaluation

#### Short-term Health Benefits and Consequences to Costs

In the short term, economic evaluation will focus on the cost-effectiveness of DMW measured over the intervention period (up to December 2020). Data on changes in outcomes from the quantitative evaluation, such as HbA_1c_ levels, will be compared against costs across population groups. Relevant costs will be direct NHS costs assessed from intervention-related costs and changes in routine health care use, as assessed from rates of primary care consultations and hospital attendance during the observation period. The unit costs of delivering traditional face-to-face behavior change interventions and psychological interventions are available in GM, enabling meaningful cost comparisons. Further unit costs will be sources of NHS reference costs and the unit costs of health and social care.

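### Medication is part of health care use as an outcome but is not among the components costed in the short-term economic evaluation, so the cost side is incomplete and could be biased in either direction.

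*Protocol article*

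**What the plan says.** **As an outcome.** Textbox 3 (Primary and secondary outcomes) lists "health care use (clinic and hospital attendance and medication use" as a secondary outcome for DMW and the two behavioral interventions. The DMW objectives in Textbox 1 use the same three components.

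**As data.** The Diabetes My Way part of the data overview describes "service use (medication, diabetes clinic attendance in primary care, and hospital visits including emergency visits" for participants. For controls, it and the NHS Digital section both list "medication, diabetes clinic attendance in primary care, and hospital visits including emergency visits". The Clinical Data section adds the drug classes: "diabetes medication, blood pressure medication, lipid lowering therapy, and service use data".

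**As a cost.** Under Short-term Health Benefits and Consequences to Costs, "Relevant costs will be direct NHS costs assessed from intervention-related costs and changes in routine health care use". The same sentence says how that use is measured: "changes in routine health care use, as assessed from rates of primary care consultations and hospital attendance during the observation period". Neither this section nor the long-term section mentions medication. The health economics objectives in Textbox 1 ask for net costs and net benefits to the health system.

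**The concern.** One construct has two definitions. Where health care use is an outcome it has three components; where it is costed it has two, and the one dropped is medication.

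This matters because the effect side of the short-term comparison is change in outcomes such as HbA1c, and the long-term model runs on changes in cardiovascular risk factors. HbA1c, blood pressure and cholesterol can all change because of prescribing. If prescribing changes differently in participants and controls, its consequences enter the effect while its cost stays out.

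The article also describes a route by which this could happen. Under Biochemical Data, participants without a recent blood sample are advised through the DMW website "to arrange a diabetes review (weight, blood pressure, smoking status, medication review, HbA_1c_, and lipids", and participants generally are advised to have repeat measurements and medication review every 3-6 months. A website message does not reach people who do not use the website.

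**Working it through.** The article states no cost figure to reproduce, so the check compares definitions and then asks how an omission would carry through.

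**1. Components of health care use, by place**

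| Place in the protocol article | Primary care | Hospital | Medication |
|---|---|---|---|
| Textbox 1, DMW objectives | clinic attendance | yes | yes |
| Textbox 3, secondary outcomes | clinic attendance | yes | yes |
| Data overview, Diabetes My Way, participants | diabetes clinic attendance | yes, including emergency | yes |
| Data overview, Diabetes My Way, controls | diabetes clinic attendance | yes, including emergency | yes |
| NHS Digital section, all patients with type 2 diabetes in the area | diabetes clinic attendance | yes, including emergency | yes |
| Short-term economic evaluation, costed use | consultations | attendance | **not listed** |

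Only the costing row omits medication. It also names a different primary care item from the data rows.

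**2. Does another cost heading pick medication up?** The other heading is intervention-related costs, which is not defined; nothing in the text extends it to prescribed drugs. The unit-cost sources named are local costs of face-to-face behavioral and psychological interventions, NHS reference costs, and unit costs of health and social care. None is identified as a source for drug prices.

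**3. Does the effect estimate exclude changes reached through prescribing?** No. The covariates listed for the HbA1c comparison are baseline weight, blood pressure, cholesterol, creatinine, cardiovascular disease and smoking. Medication is not among them. An effect that arises through later prescribing stays in the estimate, as it should for a total effect, so its cost belongs on the other side.

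**4. How the omission carries through.** Let d be the participant-minus-control difference in the change in drug cost per person, and E the difference in HbA1c change. Leaving d out alters cost per mmol/mol by d / E. The sample size section supplies E = 5 mmol/mol as the difference to be detected. The article supplies no value of d, so those below are assumptions that only show the behavior:

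- d = -100 GBP: -100 / 5 = -20 GBP per mmol/mol (a saving left out)
- d = +100 GBP: 100 / 5 = +20 GBP per mmol/mol (a cost left out)
- d = +300 GBP: 300 / 5 = +60 GBP per mmol/mol (a cost left out)

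The sign of the error follows the sign of d, and the error is zero only if d is zero.

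**The case against.** **It is only a condensed article.** Itemized resource use often sits in a full protocol or health economics plan that is not shown, and the governing phrase, direct NHS costs, is broad enough to include drugs. This would answer a silence. Here the article states how routine use will be assessed, and the stated list is narrower than its own definition. Followed as written, it leaves drugs out.

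**A reader might infer that the analysis is biased in favor of DMW.** The documents do not support that. Nothing says DMW raises prescribing. The reviews are described as in line with standard care, so controls are eligible for them too; only the prompt differs. The introduction reports a 24% diabetes remission rate and a 4.3 kg weight reduction with one of the linked programs, which could point towards less prescribing. The objection stands on direction.

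**Medication will be visible anyway.** It is collected in both groups and is a secondary outcome, so a prescribing difference could be seen. That makes the repair easy, but it does not put the cost into the ratio.

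**Two neighboring readings should not be pressed.** The Clinical Data section describes "service use data (attendance and nonattendance at diabetes clinics and emergency hospital visits", which might suggest that only emergency hospital use is available. The data overview and the NHS Digital section both specify hospital visits including emergency visits, so it is not. It might also seem that consultation rates cannot be obtained because only diabetes clinic attendance is listed. The NHS Digital section calls its list core items, so the list need not be complete; what remains is a wording mismatch.

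**Conclusion.** The inconsistency is real. The costing rule as written yields an incomplete NHS cost, because it omits a component that the article itself counts as health care use. The cost-effectiveness result would be wrong whenever prescribing changes differ between participants and controls. The documents establish neither the direction nor the size of that error, and the GBP values in the working are assumptions, not estimates.

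The conclusion rests on reading the stated cost components as complete and on undefined intervention-related costs not covering prescribed drugs. Cost-effectiveness is a secondary aim and the primary HbA1c comparison does not depend on it. Even so, the Discussion ties large claims about health care delivery to a finding of cost savings, so the cost side should be complete.

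**What to change.** In Short-term Health Benefits and Consequences to Costs, add medication to the costed components of routine health care use, so that they match Textboxes 1 and 3. Cost it from the medication data already planned for participants and controls, and name the source of drug unit costs.

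As a minor alignment, use one primary care item throughout: either add all primary care consultations to the data items for both groups, or restate the cost component as diabetes clinic attendance in primary care and limit any claim of savings to that.

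The main change costs a sentence and some extra costing work, with no new medication data. Choosing all consultations might need one more item in the NHS Digital request. The cost result may move in either direction.

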#### Long-term Health Benefits and Consequences to Costs

Short-term improvements in diabetes management can have longer-lasting impacts on health and costs. Expected reductions in rates of diabetes-related complications and death, by modifying cardiovascular risk factor levels, will be modeled using the United Kingdom Prospective Diabetes Study outcomes model [40]. Differences in quality-adjusted life years between DMW patients and those in the control group will be estimated.

### Qualitative Study

We will structure the interviews and analysis in relation to the TFA [24]. The TFA is a multifaceted construct that consists of seven domains:

Affective attitude (how an individual feels about an intervention).Burden (the perceived amount of effort it takes to engage with an intervention).Ethicality (the extent to which an intervention is congruent with an individual’s belief system).Intervention coherence (how an individual understands the aims of an intervention and how it works).Opportunity costs (the extent to which an individual needs to compromise existing benefits or values to engage with the system).Perceived effectiveness (how well an intervention achieves the desired outcomes).Self-efficacy (an individual’s level of confidence that they can engage in the behaviors required to participate in an intervention).

### Participants and Setting

#### Patients

The inclusion criteria for patients are presented in Textbox 4.

We will conduct up to 20 interviews with patients currently using DMW and 10 interviews with patients choosing not to use DMW (N=30; identified by potential participant’s clinical care team). Following the provision of information relating to the supporting interventions, potential participants will be asked by members of the clinical care team for permission to pass on their contact details to the research team who will then contact the participant directly to obtain informed consent. Purposive sampling will be used to capture a sample of participants representing a range of ethnic and socioeconomic backgrounds. Participants will be offered a choice of interview settings: at the patient’s home or in a private room at either the University of Manchester, the Manchester University NHS Foundation Trust Diabetes, Endocrinology and Metabolism Centre or at a mutually agreed public location. Alternatively, participants can choose to interview over the telephone or through videoconferencing.

Inclusion criteria for patients in the qualitative study.
**Inclusion criteria**
Age >18 years.Diagnosis of type 2 diabetes (as determined by invite to attend a specialist type 2 diabetes clinic, secondary care sites) or general practitioner records (for general practitioner practices).Registered with a general practitioner in Greater Manchester.Able to understand written English.No self-reported severe mental illness not currently managed by a physician.

#### Clinicians

The inclusion criteria for clinicians are presented in Textbox 5.

We will conduct up to 15 interviews with clinicians in groups stratified by ethnicity and indication of socioeconomic deprivation according to the lower super output area of the general practice or outpatient clinic. We will also aim to recruit clinicians working in a variety of roles. On the basis of conversations and meetings with the Greater Manchester Clinical Research Network, we anticipate the following key roles: (1) *general practice* (GPs or practice nurses with a specialist interest in diabetes) and (2) *hospital outpatient clinics* (consultants, specialist diabetes nurses, and health care assistants).

We will also conduct 2 focus groups, 1 with each participant group (patients and practitioners) involving 6-10 participants in each group (N=12-20). We will use the focus groups to further explore any issues of contention or special interest arising from the interviews in a peer group setting. The focus groups will take place in a private room at the University of Manchester.

All interviews and focus groups will be audio recorded and transcribed by an independent contractor using an intelligent verbatim approach. The independent contractor has been approved by the University of Manchester and is aware of guidelines relating to good clinical practice and confidentiality. We anticipate that the interviews will take between 30 and 60 minutes and focus groups will take approximately 60 minutes. Experienced interviewers with a background in psychology will conduct the interviews (JG and JB). Interviewers will attempt to make the interview conversational and informal, while remaining mindful of contextual features, such as power structures and professional boundaries. Data collection will be based on an interview schedule that allows for flexibility in pursuing topics of interest. Topic guides for the interviews have been developed based on the TFA [23] and the findings from the Scottish research [7,8]. We will develop topic guides for the focus groups based on findings from data generated by the interviews.

Inclusion criteria for clinicians.
**Inclusion criteria**
Age ≥18 years.A registered health care practitioner working with patients diagnosed with type 2 diabetes who have been offered Diabetes My Way intervention in Greater Manchester.Self-certified understanding of written English.

### Recruitment to the qualitative study

#### Patients

##### Overview

Patients will be recruited from 8 GP practices and 2 hospital outpatient clinics across the GM region. When engaging with patients who meet the inclusion criteria, clinicians (GPs, practice nurses, specialist diabetes nurses, health care assistants, and consultants) will invite potential participants to provide consent for the research team to contact them to provide more information about participating in the study. If patients provide consent to contact, clinicians will give them a patient information sheet to take away. Consent to contact forms will be stored safely and securely by a named individual at each recruitment site.

##### Interviews

A member of the research team will collect consent to contact forms directly from the recruiting practices and clinics weekly and contact the patients directly using the information provided, ensuring that a minimum of 24 hours has passed since consent to contact was given. The researcher will ensure that the patient has understood the participant information, answer any questions relating to participation in the research, and if the patient agrees, will then arrange a time, date, and location for the interview to take place. When interviews have been conducted with 20 patients or data saturation reached, this process will end.

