##### Focus Groups

When enough participants have been recruited to ensure data collection using interviews is complete, the process will be repeated for recruitment to the focus groups until 10 patients have taken part, at which point recruitment will cease.

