#### Clinicians

##### Interviews

In total, 15 clinicians will be recruited in three different ways:

Via the research active clinics assisting with patient recruitment.At the bimonthly GM strategic clinical network for diabetes meeting.At the launch event for the DMW system.

In each of the above settings, a member of the research team will identify key clinicians who are aware of DMW and are engaging with or are likely to engage with patients who are using or have been offered the intervention. The researcher will provide the clinician with a participant information sheet and obtain consent to contact. After a minimum period of 24 hours, the researcher will contact the clinician, ensure that they have understood the participant information, answer any questions relating to the research and then arrange a time, date, and location for the interview to take place. When interviews have been conducted with 15 clinicians or data saturation is reached, this process will end, and we will begin recruitment to the focus groups.

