##### Focus Groups

When enough participants have been recruited to ensure data collection using interviews is complete, the process will be repeated for recruitment to the focus groups until 10 patients have taken part, at which point recruitment will cease.

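### The patient-interview stopping rule (20 patients or saturation) does not fit the planned sample of up to 20 DMW users plus 10 non-users, and nothing in it secures the non-user interviews

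*Protocol article*

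**What the plan says.** The sample is set in the protocol article under Participants and Setting, Patients: "We will conduct up to 20 interviews with patients currently using DMW and 10 interviews with patients choosing not to use DMW (N=30"). The user figure is a ceiling; the non-user figure is given without one. The purposive sampling described there concerns ethnic and socioeconomic background, not whether the person uses DMW.

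Recruitment is described later, under Recruitment to the qualitative study, Patients. The Overview gives one route: "Patients will be recruited from 8 GP practices and 2 hospital outpatient clinics across the GM region". The Interviews subsection then gives the stop: "When interviews have been conducted with 20 patients or data saturation reached, this process will end". The Focus Groups subsection follows: "When enough participants have been recruited to ensure data collection using interviews is complete, the process will be repeated for recruitment to the focus groups".

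For clinicians, the target is "We will conduct up to 15 interviews with clinicians" (Participants and Setting, Clinicians) and the stop is "When interviews have been conducted with 15 clinicians or data saturation is reached, this process will end" (Recruitment, Clinicians, Interviews).

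**The concern.** The planned sample has two groups with a combined maximum of 30. The stopping rule has one count, 20, and refers simply to patients. A field team working from the recruitment section could interview 20 DMW users, close the process and move to the focus groups with no non-user interviewed. The alternative trigger, saturation, is not tied to a group either, so it could have the same effect at a smaller number.

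What is at stake is the information from people who chose not to use DMW. The Discussion (Principal Findings) says that the acceptability work could shed light on why some populations do not engage or take up the system. Strengths and Limitations looks to the qualitative results for insight into digital exclusion, which the study will not evaluate formally. Those who declined are a direct source on both questions.

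**Working it through.** **Inputs**

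| Item | Value | Place in the protocol article |
|---|---|---|
| Planned user interviews | up to 20 | Participants and Setting, Patients |
| Planned non-user interviews | 10 | same |
| Stated total | N = 30 | same |
| Stop for patient interviews | 20 patients, or saturation | Recruitment, Patients, Interviews |
| Planned clinician interviews | up to 15 | Participants and Setting, Clinicians |
| Stop for clinician interviews | 15 clinicians, or saturation | Recruitment, Clinicians, Interviews |

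**Step 1. Reproduce the stated total.** 20 + 10 = 30. This agrees with N = 30. Because the user figure is a ceiling, 30 is a maximum and not a fixed target.

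**Step 2. Compare the maximum with the stop.** 30 − 20 = 10, and 10/30 = 33%. The stop is 10 interviews below the planned maximum.

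**Step 3. Find which mixes are possible at the cap.** Let u be users and n non-users interviewed. The sample statement gives u ≤ 20 and n ≤ 10. Stopping at the cap gives u + n = 20. Hence n = 20 − u, with these extremes:

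- u = 20 gives n = 0: all planned users and no planned non-users.
- u = 10 gives n = 10: all planned non-users and half of the maximum number of users.

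So n runs from 0 to 10, and u from 20 down to 10. The combination u = 20 and n = 10 needs 30 interviews and is never reached. All 10 non-users can be interviewed within the cap only if users are held to 10 or fewer, and no text says that they will be.

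**Step 4. Look for text that restores the split.**

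- The patient inclusion criteria for the qualitative study (Textbox 4) do not mention DMW use.
- The Overview of patient recruitment describes one route, with no separate stream or quota for non-users.
- The Focus Groups subsection starts once the interviews are complete and does not say that both groups must be complete.
- The qualitative Analysis section does not define saturation by group.

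None of these resolves the mismatch.

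**Step 5. Compare with the clinician rule.** Target 15, stop 15: these agree. The mismatch is confined to the patient interviews, and the comparison suggests that the stops were meant to match the targets.

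**The case against.** The strongest reply is that the 20 in the stopping rule equals the user ceiling. The rule may simply restate that ceiling and leave the non-users out. The sample statement separately commits to 10 non-user interviews, with no ceiling wording, so a team that stopped at 20 users and no non-users would depart from that commitment. This is a fair reading, and it means that the plan should not be described as one that drops non-users. It does not remove the problem. The rule says patients, not users; if it covers users only, the non-users have no stopping rule at all.

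Several stronger readings are tempting, and the document does not support them:

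- *Non-user interviews could number as many as 20.* This takes the stopping rule in isolation. With the 10 non-users in the sample statement, the upper limit is 10.
- *The study will fall a third short of its target.* The 33% is measured against a maximum. Both passages allow fewer interviews, one through its ceiling and the other through saturation.
- *Saturation will be judged mainly on users.* The article does not say on whom it will be judged. The point is only that the clause is not split.
- *Explaining non-uptake is the purpose of the acceptability study.* Textbox 1 lists five acceptability objectives. None names non-users, and several presuppose use. Non-uptake is one strand.
- *The clinician focus-group rule is a second defect of the same kind.* That subsection ends recruitment "until 10 patients have taken part, at which point recruitment will cease", the same sentence as in the patient subsection. Participants and Setting, Clinicians already plans one focus group for patients and one for practitioners, with 6 to 10 people in each, so the intended meaning is clear. It is a clerical slip and adds no weight here.

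It can also be said that the Results report only 3 patients recruited to the qualitative study by May 10, 2021, so the cap was far from binding. That is true of the cap on that date. It also means that nearly all patient interviews were still to be done under this rule.

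**Conclusion.** The point holds as an internal inconsistency. The only stated stop for patient interviews cannot deliver the full planned sample of up to 20 users and 10 non-users: it is 10 below the maximum of 30, and at the cap between 0 and 10 of the 10 planned non-users would be interviewed. The pooled saturation clause could end recruitment earlier, before any non-user is seen.

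This rests on taking the stopping rule at its word, as a count of all patients interviewed, and on the sample statement as the plan for each group. Loss of the non-user interviews is possible, not certain; if the 20 was meant for users only, the fault is an omitted rule for non-users. The effect is limited to the qualitative study and, within it, to what can be learned about non-uptake. The HbA1c and diabetes distress comparisons and their sample sizes are untouched. It is a minor point, worth correcting because the correction is easy.

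**What to change.** In Recruitment to the qualitative study (Patients, Interviews), state the stop by group so that it agrees with Participants and Setting: up to 20 interviews with users, and 10 with patients who chose not to use DMW. Add that saturation among users does not close recruitment of non-users. At the same time, change the word for patients to the word for clinicians in the clinician Focus Groups subsection.

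The cost is two edits to the wording. No interviews are added, since all 30 are already within the plan. The recruiting sites would need to keep a separate count for each group.
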